### Cost-effectiveness analysis

The active dissemination strategies used in this project are expected to be more effective in engaging the community to implement EPICS with fidelity and thus more effective in increasing CRC screening rates. However, they will also be more expensive than the passive strategies of dissemination. Therefore, in a cost-effectiveness analysis we will determine whether the increased cost is worth the increased effectiveness. We will compare costs and outcomes of the WA, WA + TA, IP, IP + TA dissemination strategies. The cost-effectiveness analysis will be done from the perspective of a public health agency interested in disseminating EPICS (disseminator). It will thus include costs and benefits of disseminator, community coalitions, and settings. Effectiveness will be measured as described above by the increased adherence to CRC screening. Costs of the dissemination strategies will be collected using the assessment tools described above, plus study records and time logs (for example for costs of web and IP training time of personnel and materials, marketing materials, TA personnel time and expenses). From the NBLIC community coalitions we will collect data on costs incurred to engage community partners. Moreover, via periodic telephone interviews to assess the adherence to EPICS implementation protocol we will also collect information on costs related to recruiting participants and delivering the intervention. Costs of personnel time will be valued using age and gender specific wages as reported by the Bureau of Labor Statistics. Costs and outcomes occurring in year two will be discounted using a 3% discount rate. Costs and outcomes of each dissemination strategy will be compared to first eliminate dominated strategies, *i.e.*, those that are more costly than the next most effective ones. Among those that are not dominated we will calculate Incremental Cost Effectiveness Ratios (ICERs), *i.e.*, the ratio of the costs of each strategy net of those of the next less effective one, by the effectiveness. ICERs will be compared to those of similar interventions to establish cost-effectiveness. In addition, we will obtain measures of efficiency for each strategy, *i.e.*, cost per person screened, cost per community partner engaged, and other similar measures. In sensitivity analyses we will vary inputs of the analysis such as wages of personnel or number of participants per education session, to provide a range of cost-effectiveness values under different assumptions.

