**Figure 1 F1:**
[figure not shown]
CONSORT flow diagram for EPICS cRCT.

Randomization at the organizational (community coalition) level has been chosen because this will minimize contamination that may occur if individual participants are randomized. In utilizing cluster randomization, we will focus on community coalitions as the cluster for all study arms, with individuals within their target settings as the secondary unit. We will ensure balance in all four study arms by ordering them into groups based on the total number participating. A computer program generating random numbers between 1 and *n* will be used to assign community coalitions to one of four conditions: web access (WA) to facilitator training materials and toolkits without technical assistance (TA); the same as 1, but with technical assistance (TA); in-person access (IP) to facilitator training materials and toolkits without TA; and in-person access to facilitator training materials and toolkits with TA. Our multilevel approach (*e.g.*, cluster, setting, and individual) promotes widespread dissemination [13]. Community coalitions will be allocated to one of the four arms and informed consent will be obtained from community coalition members and from individual participants.

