### Toolkit

The EPICS toolkit is a package that includes facilitator training materials (manual, workshop agenda, and certificates); implementation protocol; EPICS curriculum; individual/participant educational materials; and individual/participant incentives. The toolkit was developed and pilot tested during the local and state practice demonstrations. Community coalitions randomized to passive dissemination arms will access all toolkit components except participant incentives via the web. Those randomized to active dissemination will receive all toolkit components via in-person delivery. In the case of individual/participant incentives, delivery will be via US Postal Service for community coalitions in all dissemination arms.

1. Facilitator training: Consistent with principles of Adult Learning Theory, the EPICS facilitator training workshop is skill-based, highly participatory, and provides learners with immediate opportunities to apply new skills and information [14]. A user-friendly Facilitator Training Manual has been developed and tested. The one-and-one-half-day facilitator training workshop introduces basic vocabulary, concepts, and methods of community-based cancer control and instructional strategies for African Americans of varying health literacy. Each community coalition will identify a minimum of five members, in addition to a leader, to complete facilitator training. Community coalitions randomized to passive dissemination arms will download training materials from the National Cancer Institute’s Research Tested Intervention Programs (RTIPs) website (http://rtips.cancer.gov/rtips/index.do) and conduct the training themselves, while those in active dissemination arms will be trained by EPICS developers. The facilitator training workshop consists of three modules that address: principles knowledge (*e.g.*, conceptual framework, intervention overview, and local/statewide demonstration projects); procedural knowledge (*e.g.*, how to implement the three EPICS sessions); and practical knowledge (*e.g.*, how to market the programs and complete the EPICS assessments and measures).

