### Sample size calculation

We intend to enroll 7,200 individuals in this study, with 1,800 enrolled in each study arm. This sample size is based on 20 NBLIC community coalitions randomized to four study arms (WA, WA + TA, IP, IP + TA). There will also be three settings (church, clinic, and community site) per coalition. Each community coalition will have 30 groups of individuals completing three consecutive EPICS sessions, recruiting 15 individuals per setting with an expected 25% dropout rate; thus, we anticipate that 12 of these individuals will complete all three sessions. For the EPICS cRCT, there will be (30 groups of three sessions) × (12 individuals completing all three sessions) × (20 NBLIC community coalitions) = 7,200 individuals. Based on data from a previously published study, we calculated intracluster correlation coefficient (ICC) to equal 0.0911 (9.1%) [6]. The effective sample size (ESS) was 5,645, which still has high power (>99%) with design effect of 1.2754.

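### The only stated wage basis for personnel time is age and gender, so the cost-effectiveness analysis does not capture role-related cost differences between strategies and can price the same hours differently by arm

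*Protocol article*

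**What the plan says.** The section on cost-effectiveness analysis in the protocol article gives one rule for pricing labour: "Costs of personnel time will be valued using age and gender specific wages as reported by the Bureau of Labor Statistics". It mentions no occupation, role or salary scale and exempts no group of workers.

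The same section takes the viewpoint of a public health agency that wants to disseminate EPICS, and then sets the scope: "It will thus include costs and benefits of disseminator, community coalitions, and settings". Its examples of cost items are mostly labour: "for example for costs of web and IP training time of personnel and materials, marketing materials, TA personnel time and expenses". Strategies are then screened for dominance, and incremental cost-effectiveness ratios (ICERs) are calculated for the rest. Wages of personnel are among the inputs to be varied in sensitivity analyses; how they will be varied is not stated.

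The Toolkit section says who does the training. Coalitions in the passive arms download the materials and "conduct the training themselves, while those in active dissemination arms will be trained by EPICS developers". On numbers trained: "Each community coalition will identify a minimum of five members, in addition to a leader, to complete facilitator training". On allocation, the text after Figure 1 under Trial design says: "We will ensure balance in all four study arms by ordering them into groups based on the total number participating". No balancing on characteristics of coalition members or facilitators is mentioned.

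**The concern.** The purpose of this analysis is to judge whether the extra cost of active dissemination is worth its extra effect. Much of that extra cost is time: developers train the in-person arms, TA staff serve the TA arms, and coalition members train themselves in the web arms. A wage that depends only on age and sex cannot tell these workers apart. An agency planning to disseminate EPICS pays what the job costs, so the rule fits poorly with the stated perspective.

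The rule also brings in a difference unrelated to strategy. If one arm's facilitators include more women, or are older or younger, the same hours get a different price. Such a difference would be read as a cost of the strategy.

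At stake is incremental cost, the numerator of every ICER and one of the two quantities that decide dominance.

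**Working it through.** The article reports no wage, cost or ICER, so there is no stated figure to reproduce. The wage inputs below are assumptions and the results are illustrations.

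**Inputs from the article**
- 20 coalitions in four arms. With 1,800 participants per arm and 30 × 12 = 360 per coalition, that is 1,800 / 360 = 5 coalitions per arm.
- At least 5 members plus 1 leader trained per coalition, so 5 × 6 = 30 trained people per arm.

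**1. Developer and TA time.** Let k be the job wage divided by the average wage for the worker's age and sex. The rule prices the hour at 1/k of its job cost.

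| k | Priced at (% of job cost) |
|---|---|
| 0.8 | 125 |
| 1 | 100 |
| 1.25 | 80 |
| 1.5 | 67 |
| 2 | 50 |

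The active and TA strategies look too cheap on this item if k is above 1, too expensive if k is below 1, and are priced correctly if k = 1. If this time makes up a share s of the true incremental cost and all else is priced correctly, the incremental cost changes by s × (1/k − 1). The article gives no basis for s.

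**2. Identical hours in two arms.** Set the male wage to 1 and the female wage to 1 − g, and let p be the share of women. The mean hourly price is 1 − g × p. With 30 people per arm contributing equal hours, and sex mix correlated within coalitions of six (ICC), the chance 95% difference in price between two arms, relative to the mean, is

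1.96 × g × √(2p(1 − p)/30) × √(1 + 5 × ICC) / (1 − g × p).

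For g = 0.1, p = 0.5 and ICC = 0: √(2 × 0.25/30) = 0.129, and 1.96 × 0.1 × 0.129 / 0.95 = 2.7%.

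| Wage gap g | p | ICC 0 | ICC 0.1 | ICC 0.5 |
|---|---|---|---|---|
| 10% | 0.5 | 2.7% | 3.3% | 5.0% |
| 10% | 0.7 | 2.5% | 3.1% | 4.7% |
| 20% | 0.5 | 5.6% | 6.9% | 10.5% |
| 20% | 0.7 | 5.4% | 6.6% | 10.1% |
| 30% | 0.5 | 8.9% | 10.9% | 16.7% |
| 30% | 0.7 | 8.8% | 10.8% | 16.5% |

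The ICC here is an assumed clustering of sex within coalitions, not the 0.0911 in the sample size section. Age is left out. If two arms have the same age and sex mix, the difference is zero.

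**3. Does the planned sensitivity analysis deal with this?** Suppose two workers are priced at 0.8 and 1. Raising all wages by 30% gives (0.8 × 1.3) / (1 × 1.3) = 0.8, the same relative price. A common factor therefore leaves the distortion in place. Only varying wages by role would reveal it.

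**The case against.** The case on the other side has five parts.

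- **Silence on occupation.** A condensed article need not list every unit cost, and it does not exclude a further breakdown by occupation. That is fair. But the article does state a basis, for personnel time in general, and that basis is not role.
- **Wage sensitivity analysis.** It is planned, and if wages are varied by role it would show how much the rule matters. This softens the point. It does not settle it, because the method of variation is unstated and the base case still feeds dominance and the ICERs.
- **Direction.** A reader might infer that the cost of active dissemination is understated. The document does not support this: it gives no wages, and the Community coalitions section describes members from academia, business and health care, so a large pay gap to developers is not established.
- **Demographic imbalance.** A reader might infer that identical work will cost different amounts by arm. That follows only if the staff mix differs between arms. Large chance imbalances are also unlikely under independence: for 80% against 50% women, the standard error is √(2 × 0.65 × 0.35/30) = 0.123, so the gap is 0.30 / 0.123 = 2.4 standard errors.
- **Reach of the error.** Materials, marketing, expenses, partner engagement, recruitment and delivery are costed too, and dominance depends on effectiveness as well. Cost-effectiveness is neither a primary nor a secondary outcome, and no ICER threshold is set.

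The last three limit the size and certainty of the point. None of them makes age and gender a suitable base-case price for comparing strategies that differ in who does the work.

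**Conclusion.** The point holds as a weakness in a stated analysis choice. The rule cannot capture role-related cost differences between strategies, and it allows, without making certain, a price difference between arms for identical hours.

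Developer and TA time would be priced at 125% to 50% of job cost for job wages of 0.8 to 2 times the age-sex average. The chance 95% difference in hourly price between two arms would be about 2.5% to 9% for wage gaps of 10% to 30% under independence, rising to about 5% to 17% with an ICC of 0.5 for sex mix. The wages, gaps, shares of women and clustering are all assumed.

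These percentages should not be read as errors in the ICER. They apply to personnel time only, and nothing in the document shows that a dominance ranking or an ICER would change. Reach, screening effectiveness, randomisation and sample size are unaffected. The change is worth making because it is cheap and concerns the cost contrast that the analysis exists to estimate.

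**What to change.** Replace the wage rule for the base case. Value developer and TA time at actual pay plus fringe, or at the occupation-specific wage for the role. Value facilitator and coalition time at one fixed rate per role, the same in all four arms. Keep wages by age and gender at most as a sensitivity analysis, and state that the planned sensitivity analysis varies wages by role and not only by a common factor.

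This takes about a sentence or two. Study records and time logs are already planned as cost sources; they need to identify the role of the person whose hours are logged. The downside is that the active strategies may look more expensive.

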### Community coalitions

The community coalitions that will serve as clusters in the EPICS cRCT are part of the National Black Leadership Initiative on Cancer (NBLIC), a network that was founded in 1987 and have primarily engaged in community education efforts; this history has been described elsewhere [11]. The coalitions include individuals from academia, business, health care, non-profit organizations, and other community stakeholders. Twenty of the 33 NBLIC community coalitions will be randomized as clusters in the EPICS cRCT. In developing this project, we executed Memoranda of Understanding (MOU) between the coalitions and Morehouse School of Medicine; recruited research sites and surveyed the community coalitions’ organizational characteristics.

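### The cost-effectiveness sequence attaches no sampling uncertainty to dominance or ICERs, so with five coalitions per arm a truly better, costlier strategy could be labelled dominated by chance

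*Protocol article*

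**What the plan says.** The Cost-effectiveness analysis section of the protocol article sets out an ordered procedure for the four strategies (web access or in-person, each with or without technical assistance).

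- Step 1: "Costs and outcomes of each dissemination strategy will be compared to first eliminate dominated strategies", where dominated strategies are "those that are more costly than the next most effective ones".
- Step 2: ICERs are calculated for the strategies that survive step 1.
- Step 3: "ICERs will be compared to those of similar interventions to establish cost-effectiveness".
- Sensitivity: "In sensitivity analyses we will vary inputs of the analysis such as wages of personnel or number of participants per education session". The purpose given is a range of values under different assumptions.

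On effect, "Effectiveness will be measured as described above by the increased adherence to CRC screening". On the cost of the active strategies, "However, they will also be more expensive than the passive strategies of dissemination". The section also promises efficiency measures for each strategy, such as cost per person screened.

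On the number of independent units, Community coalitions says: "Twenty of the 33 NBLIC community coalitions will be randomized as clusters in the EPICS cRCT". Sample size calculation divides these among four arms of 1,800 people each.

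**The concern.** The section exists to decide whether the extra cost of active dissemination is worth its extra effect. An in-person arm is expected to cost more than a web arm. If costs fall as expected, such an arm becomes dominated as soon as its observed screening result drops below that of a cheaper arm. It then leaves the incremental analysis before any ICER is computed, and the main question is answered by the ordering of the observed effects.

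That ordering rests on about five coalitions per arm. Nothing in the stated sequence says how sure one must be of the ordering. The named sensitivity inputs do not address this: changing wages or group size says nothing about how different the result would be with another set of coalitions. Comparison with ICERs from similar interventions adds no measure of uncertainty either. A sponsor following the text as written could report an active strategy as dominated when the data cannot separate it from a cheaper one.

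**Working it through.** **The plan's own figure.** The cost-effectiveness section states no precision figure. The nearest one is the design effect in Sample size calculation: 1.2754, with an effective sample size of 5,645. The division reproduces (7,200 / 1.2754 = 5,645). The design effect does not follow from the usual formula, 1 + (m − 1) × ICC. It equals (15 − 1) × 0.0911 = 1.2754, so the leading 1 is absent and the cluster is a recruited group of 15, not the randomized coalition. That is a separate error. It matters here because 1.2754 makes arm results look far more stable than coalition-level clustering might.

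**Inputs from the article.**
- 20 coalitions / 4 arms = 5 per arm.
- 1,800 per arm / 5 = 360 per coalition.
- ICC 0.0911.
- 33.9% screened at six months with small-group education in the earlier trial (Background).

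**Assumptions.** The true difference between arms is assumed, because no screening rates by dissemination arm are given. Other ICC values are shown as a range. The costlier arm is taken to be the truly better one. The variance is that of a single post-intervention proportion.

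**Two arms.** SE of a difference = √(2 × 0.339 × 0.661 × DEFF / 1,800). The chance that the better arm is observed as worse is Φ(−difference / SE). For a true advantage of 5 points:

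| Clustering assumption | DEFF | SE of difference (points) | Chance of reversal |
|---|---|---|---|
| Coalition of 360, ICC 0.0911 | 1 + 359 × 0.0911 = 33.70 | 9.2 | Φ(−0.05/0.0916) = 29% |
| Coalition of 360, ICC 0.05 | 18.95 | 6.9 | 23% |
| Coalition of 360, ICC 0.02 | 8.18 | 4.5 | 13% |
| Coalition of 360, ICC 0.01 | 4.59 | 3.4 | 7% |
| Session groups of 12 only, ICC 0.0911 | 1 + 11 × 0.0911 = 2.00 | 2.2 | 1.3% |
| Article's design effect | 1.2754 | 1.8 | 0.3% |

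For a true advantage of 10 points the chance is 14% at a coalition ICC of 0.0911, about 1% at 0.02 and 0.2% at 0.01.

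**Four arms.** I simulated 200,000 draws with normal arm means, the SEs above, and cost assumed to rise in the same order as true effect, so that no strategy is truly dominated. The chance that the truly best (and costliest) arm is observed below a cheaper one is:

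| True step between arms | ICC 0.0911 | ICC 0.05 | ICC 0.01 |
|---|---|---|---|
| 3 points | 50% | 42% | 20% |
| 8 points | 21% | 13% | 1% |

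With 3-point steps, the chance that at least one of the four arms is wrongly labelled dominated is 85%, 80% and 51%. That answers a different question from losing the best arm.

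**The case against.** The strongest reply is that this is a condensed article. Methods for uncertainty in ICERs (bootstrap, net benefit, acceptability curves) are commonly left to a fuller plan, and their absence is not an error. Removing dominated options before computing ICERs is also the standard order and can be repeated within each resample. Both points stand. The concern is therefore limited to the sequence as stated: it leads to a decision, and the variation it mentions is of another kind.

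A reader might infer three stronger things that the text does not support.
- That only wages and group size will be varied. The list opens with such as, so these are examples.
- That the plan commits to point estimates. The section never says so and excludes no probabilistic analysis.
- That an eliminated strategy disappears from the report. The efficiency measures are promised for each strategy, and the screening comparison has its own robust GEE inference.

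The size is also open to challenge. The ICC of 0.0911 comes from an earlier trial of 369 people in one metropolitan area, which the article does not describe as randomizing coalitions. It may not apply to coalitions of 360. The planned effect is an increase in adherence, whose variance may differ from that of a single proportion. The article says active costs more than passive but does not order the arms within each pair. These objections stand, and they are why the result is given as a range.

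**Conclusion.** The point holds in a limited form. The stated sequence carries no sampling uncertainty through dominance or ICERs, and the sensitivity examples do not supply it. If followed as written, it could label a truly better, costlier strategy as dominated by chance.

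For an assumed 5-point advantage the risk runs from about 1% (ICC confined to session groups) through 7% (coalition ICC 0.01) to 29% (coalition ICC 0.0911). It is small if true differences are around 10 points and the coalition ICC is 0.02 or less. The article does not allow a choice among these values. It would be too strong to say that the plan will discard the best strategy, or that the 85% figure measures that risk. This is worth changing, with medium confidence. It is not a fatal defect.

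**What to change.** Keep elimination of dominated strategies followed by ICERs as the base case, but state that no strategy is dropped from the conclusions on that step alone.

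- Compute cost and effect per coalition, and carry their joint uncertainty through both dominance and ICERs. Either fit a joint coalition-level or net-benefit model with delivery mode and technical assistance as factors, or resample whole coalitions within arm. Note that resampling is unstable with five coalitions per arm. The factorial model uses all 20 coalitions for each factor (10 against 10), at the price of assuming no interaction if only main effects are fitted.
- For all four strategies, report net benefit with intervals and the probability of being optimal over a stated willingness-to-pay range per additional person screened.
- Keep the wage and group-size scenarios as secondary analyses.

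The cost is analysis-plan wording and modest extra analysis of data already due to be collected. The conclusion will be less sharp. The change describes the noise; it does not reduce it.
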